+/-, signifies that these points have been rotated bidirectionally to stimulate tonification (+) and sedation (-).

By allowing the practitioners to choose the meridian channel based on each patient's symptoms, the proposed approach will provide patients with individualized therapy within a general, replicable framework. Before each treatment, a certified oriental medicine doctor will determine whether the patient’s clinical condition has changed; if so, the selection of acupuncture points will be reconsidered.

For proximal acupoints,in addition to using Sa-am acupuncture on the distal acupoints, proximal acupoints will be selected for each individualized treatment, since this is common practice for oriental medicine doctors in Korea. Based on the knee area in which each patient experiences pain, a certified oriental medicine doctor will choose two Ashi points connected to the area of pain, as well as three acupoints from the five popularly used acupoints:SP9(Yinlingquan), ST35(Dubi), EX-LE5(Xiyan), BL39(Weiyang) and EX-LE2(Heding). Since electrical stimulation can only be done in pairs, four of the five proximal acupoints will be stimulated electrically with a mixed wave frequency between 2Hz and 100Hz.

#### Standard acupuncture

The standard acupuncture treatment method for knee OA has already been described by Berman *et al*. [27]. The methods and materials used will be the same as those in the individualized acupuncture group, except for the selection of acupoints and electrical stimulation. Standard treatment will require the use in all patients of nine acupoints: SP9,GB34, ST36, ST35, EX-LE5 (Xiyan), BL60, GB39, SP6 and KI3.Electrical stimulation will also be applied to Xiyan knee points at a low frequency(8 Hz), with square biphasic pulses for 20 minutes, as previously described [27].

#### Sham acupuncture

Sham acupuncture treatment will be performed using a non-penetrating acupuncture device, Parksham acupuncture (DongBang Acupuncture Inc), consisting of a toothpick in a needle guide-tube, which is used to mimic needle insertion and withdrawal. Acupuncture-naïve patients find this method to be indistinguishable from true acupuncture [24], even though the needles do not penetrate the skin. Sham acupuncture will be applied to the same nine acupuncture points as in the standard acupuncture group. This Parksham acupuncture device has been used in several previous clinical research studies [28-30].

To simulate electrical stimulation, a mock-electrical stimulator (STN-111, StraTek Co)with the same appearance and sound as the conventional electroacupuncture device will be used, but without actual electrical stimulation.

#### No acupuncture treatment group

Patients in the control group will receive no acupuncture treatments, but will be assessed at each visit.

### Quality assurance

To ensure that treatments are of a high standard and delivered in accordance with the trial protocol, the qualifications and training certifications of each oriental medicine doctor will be thoroughly checked prior to the start of the trial. All treatments will be administered by practitioners with extensive clinical experience performing acupuncture for knee pain and the following qualifications:1. graduation from a 6-year, full-time course in oriental medicine, taught as a college program;2. certification by the Korean Ministry of Health and Welfare as an oriental medicine doctor;3. more than 1 year of postgraduate clinical training in an oriental medicine hospital; and 4. completion of the first-year residency program in the Department of Acupuncture and Moxibustion at Dongguk and Semyung University.

Prior to inclusion in this trial, each clinician will attend a 2-day training workshop on the methods of treatment. They will be taught to use the plastic Park sham needle-guiding tubes,provided written protocols and standardized recording documents. Since the interactions between oriental medicine doctors and participants can strongly influence the outcome of treatment, these interactions will be strictly limited, except when checking the patient’s health and reporting adverse events during the course of the trial.

In addition, to improve the quality of the study, outcome assessors will be blinded to group allocation and will not be involved in providing the interventions. To further ensure that the patients are blinded to group allocation, a cloth barrier will be placed onto each participant's neck to prevent the patient from seeing the acupuncture treatment taking place.

### Analysis of data

The primary efficacy endpoint of the study will be the change in Western Ontario and McMaster Universities Osteoarthritis Index (WOMAC) [31] score from before to after the 6-week, 12-visit trial.

The WOMAC is a widely used, reliable, valid and responsive measure of treatment outcomes in patients with OA of the hip or knee [31]. The WOMAC index consists of 24 questions (5 related to the amount of pain, 2 to stiffness and 17 to physical function), and takes less than 5 minutes to complete [32]. The Likert version of the WOMAC rates each question on an ordinal scale of 0 to 4, with lower scores indicating lower levels of symptoms or physical disability [33].

Secondary efficacy endpoints will include: 1. the success rate of treatment; 2. change in scores on the WOMAC pain subscales; 3. 100 mm pain VAS on walking; 4. results of a 6-minute walk test; and 5.investigator global assessment (IGA)/patient global assessment (PGA). Treatment success will be defined as ≥36% improvement in WOMAC score, and treatment failure by a change <36% in WOMAC score or a missing value [34].The 100 mm pain VAS on walking is used to evaluate the severity of pain. The patient will be asked to walk 15 m in a straight line and to determine his/her level of pain from 0 mm (absence of pain) to 100 mm (worst pain imaginable).The 6-minute walk test, which measures the distance a person can walk in 6 minutes, has been found to reliably measure functional exercise capacity and has been frequently used in OA-related trials [35,36]. For IGA and PGA, the oriental medicine doctor and the patient, respectively, will evaluate general improvements in OA pain-related symptoms, using a five-grade scale: excellent, good, fair, poor and aggravated. The 100 mm VAS on walking, WOMAC pain scale and IGA/PGA will be assessed at baseline, at each treatment session, and 12 weeks after the start of treatment. The WOMAC and 6-minute walk tests will be assessed at baseline, and after 3, 6 and 12 weeks from the start of the trial.

In addition, the patients will be asked to record their symptoms according to a VAS each morning and evening during the duration of the trial. They will also be asked to record the medications they take, such as analgesics and NSAIDs for knee pain, at the beginning of the trial, at each treatment session, at the end of treatment (week 6), and at 12 weeks after the start of the treatment (Table 2).

**Table 2 T2:** Example of outcome measurements

**Measures**		**Treatment visit**												
	**Baseline**	**1**	**2**	**3**	**4**	**5**	**6**	**7**	**8**	**9**	**10**	**11**	**12**	**Follow-up**
*Primary outcome measure*														
WOMAC^a^	x							x					x	x
*Secondary outcome measure*														
Success rate^b^	x							x					x	x
WOMAC pain(subscale)	x	x	x	x	x	x	x	x	x	x	x	x	x	x
100 mm pain VAS on walking	x	x	x	x	x	x	x	x	x	x	x	x	x	x
6-minute walk test	x							x					x	x
IGA/PGA	x	x	x	x	x	x	x	x	x	x	x	x	x	x

^a^The primary outcome is the change of WOMAC score after the 12-visit, 6-week trial.^b^Success will be defined as ≥36 % improvement in WOMAC score, and failure as <36 % improvement or missing values.IGA, investigator global assessment; PGA, patient global assessment; VAS, visual analogue scale; WOMAC, Western Ontario and McMaster Universities Osteoarthritis Index.

Any reported adverse events will be recorded throughout the study, and vital signs will be monitored at each visit.

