**Methods/Design:**

The study is designed to be a parallel, patient- and assessor-blind, randomized controlled trial (RCT). A total of250 patients with knee osteoarthritis (OA) will be recruited from two independent hospitals, Semyung University Oriental Medicine Hospital in Chung-ju and Dongguk University Oriental Hospital in Ilsan, South Korea. Patients will be randomly allocated into four treatment groups: 1. individualized, meridian-based syndrome differentiation and Sa-am acupuncture treatment;2. standard acupuncture treatment;3. sham acupuncture treatment; and 4. no acupuncture treatment. Patients in groups 1 to 3 will be treated by certified oriental medicine doctors twice a week for 6 weeks. The primary outcome measure will be the self-reported total Western Ontario and McMaster Universities Osteoarthritis Index (WOMAC) score change. The trial will also include secondary outcome measures.

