### Randomization and blinding

Patients will be randomized by an independent statistician using a computerized, random-number generator through the block-randomization method of SAS version 9.1(SAS Institute Inc, Cary, NC, USA) for sequence generation. Separate randomization files will be created for each of the two sites. Allocations will be concealed using sealed, opaque envelopes. After the assessor has screened the patient for inclusion and the patient has signed the informed consent form, the next envelope in the sequence will be provided, immediately prior to treatment, to the certified oriental medicine doctor who will perform acupuncture. By this method, a total of 250 participants will be randomly assigned to the four groups. Although all patients and their screening assessors will be blinded to treatment, the certified oriental medicine doctor applying acupuncture will not.

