## Discussion

The individualized acupuncture treatment method proposed in this study, consisting of meridian-based syndrome differentiation and Sa-am acupuncture, is not only the most commonly method used by certified oriental medicine doctors in Korea to treat patients with OA [21,25], but can be generalized for widespread use in the future. In this trial, we will evaluate the efficacy of this individualized treatment method by comparing it with standard, sham and non-treatment groups.

The acupuncture methods employed in this study are the closest to actual clinical practice and can be used in future studies. Moreover, the techniques of meridian based and Sa-am acupuncture that we will use in this study are based on the consensus of many certified oriental medicine doctors in Korea. In addition, we will strive to conduct a high quality, single-blinded clinical trial by ensuring that the assessors and participants are not informed of the type of treatment, by using a variety of controls including Park sham acupuncture, and providing trial-specific training of the exact methods used to well-qualified and certified oriental medicine doctors.

In conclusion, this research involves three different controls, and it will help elucidate the efficacy of individualized acupuncture versus standard, sham and no acupuncture groups.

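### The IGA is assigned to the oriental medicine doctor, most naturally the unblinded treating practitioner, which conflicts with the statement that outcome assessors are blinded and do not treat

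*Protocol article*

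**What the plan says.** Four parts of the protocol article bear on this point.

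- **Analysis of data** lists the IGA, paired with the patient global assessment (PGA), as the fifth secondary efficacy endpoint and names the raters: "For IGA and PGA, the oriental medicine doctor and the patient, respectively, will evaluate general improvements in OA pain-related symptoms". The scale has five grades, from excellent to aggravated. On timing, "IGA/PGA will be assessed at baseline, at each treatment session, and 12 weeks after the start of treatment". Table 2 shows the same schedule.
- **Randomization and blinding** hands the next envelope over "immediately prior to treatment, to the certified oriental medicine doctor who will perform acupuncture". It then says that patients and screening assessors are to be blinded, but "the certified oriental medicine doctor applying acupuncture will not".
- **Quality assurance** states, with no exception, that "outcome assessors will be blinded to group allocation and will not be involved in providing the interventions".
- **Abstract, Study design and Discussion** present the trial as blinded for assessors as well as patients. The Discussion speaks of "ensuring that the assessors and participants are not informed of the type of treatment".

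**The concern.** Whoever grades an efficacy endpoint is the outcome assessor for that endpoint. If the doctor who opens the envelope and places the needles also scores the IGA, the rating rule and the blinding rule cannot both be followed.

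The IGA is vulnerable because it is one person's overall judgement of improvement, with no physical measurement behind it. A rater who knows the arm, and who gave the treatment, may grade in line with expectation. In the individualized arm the doctor also reviews the patient's condition before each session and may choose the points afresh, so the same person would be grading the result of their own choices. The quality assurance section itself recognises that contact between doctor and patient can influence outcome, and it restricts that contact.

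At stake is an efficacy result that would be reported under a blinding claim it does not meet.

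**Working it through.** The question is mainly one of reading, so the statements are set side by side.

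1. **Who is the oriental medicine doctor?** Where the article describes trial staff, the term means the practitioner who treats. The abstract says "Patients in groups 1 to 3 will be treated by certified oriental medicine doctors twice a week for 6 weeks". The sections on randomization, individualized acupuncture and quality assurance use it the same way. Where a blinded rater is meant, the article says assessor. The term is not confined to trial staff, though: the Background, the Treatment section, the account of the survey and the Discussion also use it for the profession at large.

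2. **When is the IGA scored?** At each treatment session, among other times. The treating doctor is present then.

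3. **Is that doctor blinded?** No. The doctor who applies acupuncture receives the envelope and is expressly left out of the blinding.

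4. **Does the article describe another doctor, blinded and not treating, who scores the IGA?** No.

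Steps 1 to 4 make the treating practitioner the natural reading. On that reading the Analysis of data section contradicts the Quality assurance section.

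**Number of ratings exposed.** Table 2 schedules 1 baseline + 12 visits + 1 follow-up = 14 IGA ratings. The envelope is handed over after screening and consent, immediately before treatment, so the baseline rating probably precedes it. That leaves 14 − 1 = 13 at most. If the visit 1 rating is also made before the envelope is opened, the number is 12.

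**Reach into the other endpoints.**

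- The WOMAC (total, pain subscale and the success rate derived from it), the walking VAS and the PGA are scored by the patient.
- The 6-minute walk test has no named rater, so the general statement on blinded assessors still covers it.

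**Sample size.** It rests on the WOMAC alone and reproduces from the stated inputs (SD 3.35, difference 2.34, two-sided 0.05, 80% power):

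- n per arm for two equal arms = 2 × (1.960 + 0.842)² × 3.35² / 2.34² = 2 × 16.09 = 32.2, rounded up to 33 for the smallest arm.
- With 2:2:1:1 allocation, 33 × 6 = 198, as stated.
- For 20% dropout, 198 / 0.8 = 247.5, so 248 against the stated 250.

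The choice of IGA rater enters none of these figures.

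**The case against.** The strongest reply is that the article never says the treating doctor scores the IGA. It says only the oriental medicine doctor, and the exclusion from blinding is worded for the doctor applying acupuncture. A second doctor, not treating and kept blind, would satisfy all three sections at once, and the full protocol, which is not shown, may name one. This stands to the extent that the rater's identity is an inference. It does not remove the point. The article mentions no such person, uses the term for the treating staff when it describes trial conduct, and ties the rating to the treatment sessions. If a separate doctor is intended, a sentence saying so is still needed.

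A second reply is that the reach is narrow: the IGA is one half of the last of five secondary items, and the plan gives it no confirmatory role. That is correct and limits the consequence.

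A reader might also infer that in the no-acupuncture arm the rater knows the allocation because there is no treatment session. The document does not support this. Those patients are still assessed at each visit, nobody needles them, and the article does not say who scores their IGA. An assessor kept away from the treatment sessions need not know whether one took place.

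**Conclusion.** The point holds as an inconsistency to be reconciled. The IGA is assigned to a role that is most naturally the unblinded practitioner, against an unqualified statement that outcome assessors are blinded and do not treat. On that reading, up to 13 post-baseline ratings per patient of a subjective secondary endpoint are open to detection bias. This rests on two assumptions: that the rater is the treating doctor, and that the baseline rating is made before the envelope is opened.

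Three stronger readings should be resisted.

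- **All 14 ratings are affected.** The order of consent, envelope and treatment makes this unlikely for baseline.
- **The bias can be given a size.** One could suppose that 10 to 20% of patients in the real-acupuncture arms are graded one step too high and read off a shift of 10 to 20 percentage points. The document gives no such rate and fixes no IGA cut-point. Those figures would be a ceiling, reached only if every upgrade crossed the chosen cut.
- **The trial's main result is compromised.** The primary endpoint is patient-reported, and neither its ANCOVA nor the sample size depends on who scores the IGA.

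**What to change.** Amend the Analysis of data section so that the blinded, non-treating outcome assessor already described under Quality assurance scores the IGA in all four arms, without access to treatment notes. Patients in every arm are already assessed at each visit, so no visit is added.

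If that assessor cannot be present at every visit, declare the IGA an unblinded outcome and limit the blinding statements in the abstract, Study design, Quality assurance and Discussion to the other outcomes.

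In either case, report IGA ratings already made by treating doctors as unblinded. The Trial status section says that enrollment was still under way, so a change could still protect later ratings.

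The cost in text is a sentence or two and a reassigned rating form. There are two practical costs. Ratings made before and after the change may not be comparable. The blinded assessor must also be available, and suited to making a global clinical judgement, at each visit where the IGA is scored; the article does not say whether this is so.

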### Sample size

The primary efficacy parameter is change in WOMAC score from baseline to the end of treatment after 6 weeks. The standard deviation (SD) of the WOMAC score is 3.35 [27]. In calculating the appropriate sample size for this study, we sought to obtain a more conservative SD, with a true mean difference of 2.34.

With *μ*_1_ and *μ*_2_ representing the mean WOMAC scores for the test and control groups, respectively, the null-hypothesis 

$$H_{0}:\mu_{1}-\mu_{2}=0$$

 will be tested versus the alternative hypothesis 

$$H_{1}:\mu_{1}-\mu_{2}\neq 0$$

Using these hypotheses, we calculated the sample size needed to achieve 80% power using the equation: 

n=Zα/2+Zβ2σ2μ1-μ22.

To show that the individualized treatment group is not equal to the control groups, patients will be randomized 2:2:1:1 to the individualized treatment group, standard treatment group, sham group and untreated group, respectively. Using these assumptions and specifications, a sample size of 198 individuals (66:66:33:33) will provide a power of 80% at a significance level of 0.05. To allow for a 20% dropout rate, a slightly higher number, 250 patients, will be randomized in the trial.

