### Statistical analysis plan

All statistical analyses will be performed using SAS version 9.1 or a later version. All statistical tests will be two-sided and the level of significance will be set at 0.05. The last observation carried forward (LOCF) method will be used to input data with dropouts. Continuous variables will be expressed as mean ± SD, and categorical variables as number and percentage.

The primary endpoint will be compared in the four groups by analysis of covariance (ANCOVA),with treatment means adjusted to baseline WOMAC scores as a covariate. Confidence intervals will be derived from ANCOVA. Repeated measures analysis of variance (ANOVA) will also be used to analyze primary and secondary efficacy variables. Categorical data will be analyzed using Pearson’s chi-square test or Fisher’s exact test.

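### The sample size rests on an SD of 3.35 and a difference of 2.34 on an unnamed WOMAC scale; both look too small for the 0 to 96 total, so 80% power is not established for the primary endpoint

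*Protocol article*

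**What the plan says.** The abstract of the protocol article defines the endpoint: "The primary outcome measure will be the self-reported total Western Ontario and McMaster Universities Osteoarthritis Index (WOMAC) score change". The Analysis of data section describes the instrument: "The WOMAC index consists of 24 questions (5 related to the amount of pain, 2 to stiffness and 17 to physical function"). It adds: "The Likert version of the WOMAC rates each question on an ordinal scale of 0 to 4". The range of the total is not printed, but 24 × 4 = 96. The same section lists the WOMAC pain subscale separately, as a secondary endpoint.

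The Sample size section names the change in WOMAC score at 6 weeks as the primary parameter and continues: "The standard deviation (SD) of the WOMAC score is 3.35 [27"]. Of the difference it says "we sought to obtain a more conservative SD, with a true mean difference of 2.34". No second SD is given. It concludes that "a sample size of 198 individuals (66:66:33:33) will provide a power of 80% at a significance level of 0.05", and raises the number to 250 for 20% dropout.

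The section does not say whether 3.35 and 2.34 refer to the total or to a subscale, or whether 3.35 is the SD of a score or of a change.

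**The concern.** The power statement is made for the primary endpoint, so its inputs should be on the scale of that endpoint. An SD of 3.35 is 3.5% of a 0 to 96 range (3.35/96), and the difference of 2.34 is 2.4% of it (2.34/96). So small a spread would mean that patients hardly differ in total score.

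If the real SD of the total is larger, the trial cannot detect 2.34 points with the power it claims. A non-significant result could then be read as ruling out a difference of that size when it does not. A reader also cannot tell from the article what difference on the total score the trial was built to detect.

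**Working it through.** **Inputs.** From Sample size: SD 3.35, difference 2.34, power 80%, evaluable arms 66:66:33:33. From Statistical analysis plan: "All statistical tests will be two-sided and the level of significance will be set at 0.05". From Analysis of data: 24 items, 5 of them on pain, each scored 0 to 4. Inter-item correlations and SDs of the total are not in the article. They are assumed below and shown as ranges.

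**1. The plan's own figure.** The usual two-sample formula gives, per arm,

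n = 2 × (1.960 + 0.842)² × 3.35² / 2.34² = 32.2, rounded up to 33.

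The 2:2:1:1 allocation then gives 66:66:33:33 = 198, and 198/0.8 = 247.5, so 248, close to the stated 250. The figures reproduce, so the question is the scale of the inputs. On these inputs 33 v 33 has 81.0% power, and the planned 66 v 33 and 66 v 66 have 90.6% and 98.0%.

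**2. Does 3.35 fit a 24-item total?** For a sum of m items with common SD s and mean correlation ρ,

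SD(sum) = s × √(m + m(m − 1)ρ).

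The item SD needed for a sum with SD 3.35 is:

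| Sum | Assumed ρ | √(m + m(m − 1)ρ) | Item SD needed |
|---|---|---|---|
| 24 items | 0 | 4.90 | 0.68 |
| 24 items | 0.3 | 13.77 | 0.24 |
| 24 items | 0.5 | 17.32 | 0.19 |
| 5 items (0 to 20) | 0.3 | 3.32 | 1.01 |

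Questions about one painful knee can be expected to correlate. Item SDs of 0.19 to 0.24 are hardly possible for whole-number answers from 0 to 4 unless nearly all patients answer alike. The formula applies equally to changes in the items. For a 5-item sum, the same 3.35 needs an ordinary item SD of about 1.0.

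**3. How far can the SD rise before 80% is lost?** With the difference held at 2.34,

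SD limit = 2.34 / [(1.960 + 0.842) × √(1/n₁ + 1/n₂)].

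- 66 v 33: √(1/66 + 1/33) = 0.2132, limit 3.92.
- 66 v 66: √(2/66) = 0.1741, limit 4.80.

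**4. Illustration with assumed SDs of the total.** Power = Φ(2.34 / [SD × √(1/n₁ + 1/n₂)] − 1.960). Detectable difference at 80% power = 2.802 × SD × √(1/n₁ + 1/n₂).

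| Assumed SD | Power for 2.34, 66 v 33 | Power for 2.34, 66 v 66 | Detectable, 66 v 33 | Detectable, 66 v 66 |
|---|---|---|---|---|
| 10 | 19% | 27% | 6.0 | 4.9 |
| 15 | 11% | 14% | 9.0 | 7.3 |
| 20 | 8% | 10% | 11.9 | 9.8 |

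**5. Baseline adjustment.** The planned ANCOVA uses the baseline-adjusted SD, which is smaller. With an assumed score SD of 10 and baseline correlation of 0.7 it is 10 × √(1 − 0.49) = 7.1, still above both limits in step 3.

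**The case against.** Four objections deserve an answer.

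- **Source of the figures.** A reader might infer from step 2 that 3.35 and 2.34 were taken from the pain subscale. The article does not show this. It attributes 3.35 to the WOMAC score and cites a source that is not at hand. The size of the figure suits a 5-item sum, but that is not proof.
- **Underpowered trial.** A reader might also infer that the trial is underpowered. That does not follow. Power depends on the ratio 2.34/3.35 = 0.70. If the total showed the same standardized effect (7.0 points at SD 10, 14.0 at SD 20), power at 66 v 33 would still be 90.6%. The low percentages in step 4 raise the SD and leave 2.34 fixed, so they hold only if 2.34 points on the total is really the target. This objection stands as a limit on the size of the problem. It does not rescue the 80% claim, because the article states a difference in points and neither claims nor supports an effect of 0.70 SD on the total.
- **Responder rule.** It is tempting to set 2.34 against the protocol's rule of at least 36% improvement. That comparison is not valid: the rule is a within-patient threshold and 2.34 is a between-group mean difference. It forms no part of this point.
- **Conservative SD.** The remark about a more conservative SD may mean that 3.35 is itself the cautious choice. That reading is possible, and nothing here depends on it.

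**Conclusion.** The point holds as a problem of unidentified and implausible inputs, with no error in the arithmetic. The scale of 3.35 and 2.34 is not named, and 3.35 is too small to be credible for a 24-item total unless the items are almost uncorrelated or patients almost identical. The stated 80% power is therefore not established for the primary endpoint.

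One result needs no assumption about the SD of the total: for 2.34 points, power falls below 80% once the relevant SD exceeds about 3.9 (66 v 33) or 4.8 (66 v 66). The implausibility of 3.35 rests on assumed inter-item correlations of 0.3 to 0.5. The power ranges of about 19% to 8% and 27% to 10% rest on assumed SDs of 10 to 20 and a fixed 2.34, and are illustrative only. The true power for a relevant difference on the total cannot be worked out from the article.

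**What to change.** Rewrite the Sample size paragraph on the scale of the primary endpoint:

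1. State which WOMAC scale 3.35 and 2.34 come from, and whether 3.35 is the SD of a score or of a change. If they belong to a subscale, stop presenting them as the basis for the total.
2. Give the SD of the 6-week change in total WOMAC or, better matched to the planned ANCOVA, the baseline-adjusted SD. It can come from a source for the total or from blinded pooled data, since the Trial status section says enrollment continues.
3. Name and justify a target difference on 0 to 96. A detectable difference worked back from the sample size does not replace one.
4. Keep n = 250. Replace the 80% claim by the power for that target, and give the detectable difference for 66 v 33 and 66 v 66, for example 9.0 and 7.3 points at an assumed SD of 15.

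The cost is one recalculation, some rewording and, if used, a blinded look at the pooled variance. No extra patients are needed. The stated sensitivity may become less favorable.
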